### Data management

Electronic Medical Record Form (ECRF) will be utilized to collect data. All data will be stored in a highly secured database to ensure safety. The data will be backed up periodically (every 4 weeks). Electronic signed consent forms will be stored in our online assessment platform. The printed version will be stored in the locked room in our department. The raw data and all steps taken in the analysis will be documented in ECRF and SPSS to enable future researchers to understand and reuse the data. All data will be retained until 10 years after the completion of the study. Participant information will be protected and participant anonymity will be ensured to protect the rights of each participant.

## Statistical methods

### Statistical methods for primary and secondary outcomes

The statistical analyses will follow the intention-to-treat (ITT) principle. Missing values will be handled using a last observation carried forward (LOCF) analysis. Descriptive statistics at baseline will be computed using frequencies and percentages for categorical variables, means with standard deviations (SD) or medians with lower and upper quartiles for continuous variables. Tests of statistical significance between groups will be made. Clinical remission rate of insomnia in week 8 and week 20 will be calculated. All analyses will be conducted using IBM SPSS 25.0. A two-tailed p-value < 0.05 will be considered statistically significant.

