1. The iMBCT-I will improve sleep quality, level of mindfulness, quality of life and attitudes towards traditional psychotherapy and online psychotherapy by the end of the intervention (week 8).2. The iMBCT-I will decrease dysfunctional beliefs about sleep, anxiety and depression by the end of the intervention (week 8).3. The effect of the iMBCT-I will be maintained at the scheduled follow-up assessment (week 20).4. Mindfulness levels, attitudes towards traditional psychotherapy or online psychotherapy at baseline will have an influence on both the short-term (week 8) and long-term (week 20) effects of the iMBCT-I.

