### Criteria for discontinuing or modifying allocated interventions

If a participant withdraws informed consent or experiences a serious adverse event (such as self-harm or impulsive behaviors) during the study, they will be immediately withdrawn from the trial and provided with appropriate treatment as necessary.

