### Sample size

With reference to the results of a large-scale randomized controlled trial conducted by Lee M. R. which compared the effects of online CBT-I with SHE on chronic insomnia patients, we estimated that the ISI score reductions in the iMBCT-I group and the SHE group were 7.7 and 3.1, respectively, with a common standard deviation of 5.5 (42). Assuming an alpha level of 0.05 and a power level at 0.9, the calculated minimum sample size was 30 participants per group. Estimating a dropout rate of 20%, we plan to recruit 80 participants in total.

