#### Secondary outcome analysis

Changes between groups in scores of PSQI, FFMQ, PHQ-9, GAD-7, SF-12, ATSPPH-SF and DBAS-16, insomnia remission rate and all sleep parameters values from baseline to week 8 will be evaluated using paired t-tests (for normally distributed data)/Mann-Whitney U tests (for non-normally distributed data). Mixed-effect models for repeated measures will be used to evaluate the effects of the online MBCT-I on scores of ISI, PSQI, FFMQ, PHQ-9, GAD-7, SF-12, ATSPPH-SF and DBAS-16 as well as all sleep parameters values over time (from baseline to week 20). The model will include treatment group, time, treatment-by-time interaction and baseline covariates.

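### Last observation carried forward turns every missing week-8 ISI into zero change, which the sample size does not allow for and which can bias the primary effect in either direction

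*Protocol article*

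**What the plan says.** Under statistical methods for primary and secondary outcomes, the protocol article commits to intention to treat ("The statistical analyses will follow the intention-to-treat (ITT) principle") and then gives one missing-data rule: "Missing values will be handled using a last observation carried forward (LOCF) analysis". The rule is not limited to any outcome, visit or model.

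Table 1 schedules the ISI at screening and at weeks 0, 8 and 20. The primary analysis section uses the change in ISI from baseline to week 8 as the dependent variable, with arm as the only independent variable. The one analysis labelled as a sensitivity analysis adds covariates and does not deal with missing data.

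The sample size section assumes ISI reductions of 7.7 (iMBCT-I) and 3.1 (SHE) with a common SD of 5.5. It continues: "Assuming an alpha level of 0.05 and a power level at 0.9". This gives 30 per group, followed by "Estimating a dropout rate of 20%, we plan to recruit 80 participants in total".

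For the course to week 20, the secondary analysis section says: "Mixed-effect models for repeated measures will be used to evaluate the effects of the online MBCT-I on scores of ISI", together with the other scales. The third secondary hypothesis is that the effect persists to week 20. Separately, the section on discontinuing or modifying interventions says of participants with a serious adverse event, or who withdraw consent, that "they will be immediately withdrawn from the trial and provided with appropriate treatment as necessary".

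**The concern.** Between baseline and week 8 there is no intermediate ISI to carry. At the primary time point LOCF is therefore baseline carried forward: each person with a missing score enters the analysis as having not changed at all. That conflicts with the plan's own expectation that both arms improve.

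Three things are at stake.

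- **Size and power of the primary comparison.** The sample size inflates for dropout as if dropouts leave the analysis, whereas the analysis keeps them in at zero.
- **Direction of bias.** Zero is further from the expected 7.7 than from the expected 3.1, so the effect depends on which arm loses more people. Eight weekly sessions with homework against a single session makes unequal loss plausible, although the document gives no figure for it.
- **Week 20.** Someone seen at week 8 and then lost cannot relapse in the analysed data, while someone lost before week 8 is held at baseline throughout.

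A mixed model can use incomplete records directly under missing at random. If the gaps are first filled by LOCF, as the unrestricted rule implies, that benefit is lost.

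**Working it through.** **Inputs.** From the sample size section: mean reductions 7.7 and 3.1 (difference 4.6), SD 5.5, alpha 0.05, power 0.90, 30 per group, 20% dropout, 80 recruited. Two-sided testing comes from the statistical methods section ("A two-tailed p-value < 0.05 will be considered statistically significant"). With 1:1 allocation I take 40 per arm; simple randomisation may give slightly different numbers.

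**The plan's own figure.** n per arm = 2 × (1.960 + 1.282)² × (5.5/4.6)² = 30.04, so the stated 30 is reproduced to rounding. Dropout: 60/0.8 = 75, and 80 exceeds this. With 20% lost, 32 per arm are observed: SE = 5.5 × √(2/32) = 1.375 and power is 0.909 (two-sample t).

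**Week 8 under LOCF.** Let a share q of an arm be missing, independently of outcome, and set to zero change.

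- Arm mean = (1−q) × μ
- Arm variance = (1−q) × 5.5² + q(1−q) × μ²

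At q = 0.20 in both arms:

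- Means: 0.8 × 7.7 = 6.16 and 0.8 × 3.1 = 2.48, difference 3.68
- Variances: 24.2 + 0.16 × 59.29 = 33.69 and 24.2 + 0.16 × 9.61 = 25.74
- SE = √((33.69 + 25.74)/40) = 1.219
- Power = 0.847 (t) or 0.855 (normal); simulation gave 0.848

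Power by equal missing share at week 8 (normal approximation):

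| Missing | Difference | Power |
|---|---|---|
| 0% | 4.60 | 0.962 |
| 10% | 4.14 | 0.920 |
| 12% | 4.05 | 0.908 |
| 13% | 4.00 | 0.903 |
| 14% | 3.96 | 0.896 |
| 20% | 3.68 | 0.855 |

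The t-based values cross 0.90 slightly earlier, between 12% and 13%. At 20% missing, LOCF would need 47 per arm for 90% power.

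**Unequal dropout (assumed splits, same overall 20%).**

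| iMBCT-I / SHE missing | Difference | Power (t) |
|---|---|---|
| 30% / 10% | 0.7 × 7.7 − 0.9 × 3.1 = 2.60 | 0.54 |
| 10% / 30% | 0.9 × 7.7 − 0.7 × 3.1 = 4.76 | 0.98 |

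If instead both arms truly improve by 3.1, a 30%/10% split in either direction creates a false difference of 0.2 × 3.1 = 0.62 against an SE of 1.13. The two-sided type I error is then 0.084 by calculation and about 0.087 by simulation. With equal 20% dropout it stays at 0.05.

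**Week 20.** Assume for illustration that the true difference is 4.6 at week 8 and 2.3 at week 20. Let p be the share lost before week 8 and f the share lost after it, equal in both arms. LOCF then gives (1−p−f) × 2.3 + f × 4.6:

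| p | f | LOCF difference | Against the assumed 2.3 |
|---|---|---|---|
| 0% | 20% | 2.76 | 20% too large |
| 10% | 10% | 2.30 | no net bias |
| 15% | 5% | 2.07 | 10% too small |
| 20% | 0% | 1.84 | 20% too small |

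**The case against.** Much can fairly be said for the plan.

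**Power.** The document does not say when the 20% is lost. If half goes after week 8, primary power under LOCF is still about 92%. A reader might infer that the stated 90% is lost in any event; it is lost only above roughly 12–13% missing at week 8, and the loss at 20% is moderate. This stands.

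**Week 20.** A reader might infer that LOCF builds the maintenance hypothesis into the data. That is true only of people lost after week 8. Those lost earlier pull the other way, and an even split of the 20% cancels exactly in the illustration above. The documents do not support a claim in one direction.

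**Standard errors.** A reader might infer that the week-8 standard error is simply wrong. With equal dropout it matches the sampling variation of the diluted estimate (1.21 against 1.22 in simulation). The trouble is what is being estimated: in simulation the nominal 95% interval covers the assumed 4.6 in only 88% of trials at 20% missing.

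**The 42% figure.** The introduction reports that 42% completed at least six face-to-face sessions. That is attendance, not missing outcomes, so it cannot be read as a dropout rate. Online assessment with notifications and phone reminders may keep losses low. Mandatory questions, however, prevent only missing items within a form, not missed assessments, and the plan itself budgets for 20%.

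**The unseen analysis plan.** It could hold more detail, and the trial calls itself exploratory. But LOCF is a stated, unrestricted choice, so replacing it is not a request for detail left elsewhere. That the mixed models would run on LOCF-filled data is an inference, though the natural reading of the rule.

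**The remedy.** A model with weeks 8 and 20 as responses learns nothing about outcome from people missing at both visits. For early dropout it is close to an analysis of available cases, valid only under missing at random. This also stands and is why a further sensitivity analysis is needed.

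**Conclusion.** The point holds. The only stated missing-data rule assigns zero change to every missing week-8 ISI, against the plan's own assumed improvements, and it is inconsistent with how the sample size treats dropout.

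- If the full 20% per arm is missing at week 8, independently of outcome, the expected difference falls by 0.92 points (4.6 to 3.68) and power is about 85%, against about 91% for 32 observed per arm.
- With unequal dropout the estimate can move down or up (2.60 or 4.76 under the assumed 30%/10% and 10%/30% splits), and type I error reaches about 8–9% when both arms improve by 3.1. LOCF is therefore not reliably conservative. These splits are assumptions, not figures from the document.
- At week 20 there is bias of unknown net direction, depending on when dropout occurs.

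The section on discontinuing or modifying interventions is a secondary matter. Removing participants from the trial after a serious adverse event sits uneasily with the intention-to-treat commitment as regards outcome collection, and the two passages must be reconciled. Its numerical effect is probably small, since the document reports no serious adverse events with MBCT-I in previous studies.

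**What to change.** - Replace LOCF as the main method. Use the mixed model already planned for ISI, fitted by likelihood to unimputed data, with weeks 8 and 20 as responses and arm, visit, arm-by-visit and baseline ISI as terms. Take the primary estimate from the week-8 contrast. Multiple imputation by arm is an acceptable alternative.
- Keep LOCF only as a sensitivity analysis, described at week 8 as what it is: baseline carried forward.
- Add one sensitivity analysis for data not missing at random, for example a delta adjustment.
- Reconcile the trial-withdrawal wording with the intention-to-treat statement, so that it is clear whether outcome assessments are still sought from participants who stop.

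The cost is a change of wording and modest extra analysis. The main analysis will then rest on missing at random, which the data cannot confirm. No change to sample size or visits is needed: 32 observed per arm gives about 91% power on the plan's assumptions.

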#### Primary outcome analysis

Changes between groups in ISI scores from baseline to week 8 will be evaluated using paired t-tests (for normally distributed data) or paired Mann-Whitney U tests (for non-normally distributed data). The between group effect sizes (Cohen’s d) will be calculated using the mean differences from baseline and the SDs of the two groups at week 8.

A Univariable linear regression will be conducted to evaluate the effect of MBCT-I on ISI score reduction. The change in ISI scores from baseline to week 8 will be used as the dependent variable, while the intervention group (MBCT-I vs. SHE) will be included as the independent categorical variable. The regression coefficient (B) will represent the estimated effect of MBCT-I on ISI score reduction.

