Nevertheless, the large and widespread population suffering from insomnia and limited mental health resources have hindered the adoption of traditional face-to-face psychotherapies among CID patients in China (29). Although CBT-I has been widely acknowledged as a golden approach for treating CID, obstacles such as a lack of skilled professionals, lengthy treatment cycles and high cost have limited the promotion of CBT-I in clinical implementation. Fewer than 1% of CID patients gained access to CBT-I (30). To address these challenges, internet-based CBT-I (iCBT-I) has emerged and garnered significant attention in recent years. Several recent meta-analyses have shown that therapist-guided iCBT-I not only yields outcomes comparable to those of face-to-face CBT-I for CID but also alleviates the economic burden for patients and saves medical resources (31–34). Therefore, therapist-guided iMBCT-I is expected to be a promising treatment approach for CID patients with high efficacy and accessibility. However, the effectiveness of guided iMBCT-I has not yet been tested in CID patients.

This is one of the earliest randomized controlled studies to evaluate the effectiveness of therapist-guided iMBCT-I in CID patients by comparing it to that of sleep hygiene education (SHE). In this study protocol, we will simplify the standardized MBCT format, reducing the session duration from 2.5 hours to a more manageable 1.5 hours, which may enhance the compliance and engagement of participants. The iMBCT-I program is not only tailored to the context of China but also more accessible for individuals seeking online interventions. If proven effective, this study will provide valuable evidence for clinical practitioners, therapists, and patients considering a novel psychotherapeutic option and offers insights for technicians involved in the future implementation of self-guided iMBCT-I applications.

The primary outcome is insomnia severity. The secondary outcomes include sleep quality; sleep parameters recorded via a sleep diary and actigraphy; the level of mindfulness; dysfunctional beliefs about sleep; anxiety; depression; quality of life; and attitudes towards traditional psychotherapy and online psychotherapy. Data about intervention satisfaction and suggestions will be collected.

The primary hypothesis for this trial is that the iMBCT-I will reduce insomnia severity by the end of the treatment (8 weeks).

The secondary hypotheses for this trial are as follows:

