## Methods

### Trial design

This is a prospective, parallel-group, exploratory randomized (1:1 allocation ratio) controlled study. This study will be carried out following the CONSORT 2010 statement, as shown in **Figure 1**. Initially, interested participants will undergo preliminary screening via an online questionnaire. Those meeting the criteria will be further evaluated via video calls by two psychiatrists to determine eligibility for inclusion. All eligible participants will subsequently electronically sign informed consent forms before baseline assessment and intervention. After the intervention concludes, participants will be required to complete two assessments: one immediately post-intervention (8 weeks) and another three months thereafter (20 weeks). The signing of informed consent and all questionnaire assessments will be completed on Questionnaire Star (a popular online survey platform in China), and the intervention programs will take place at Tencent Meeting (a widely used online conferencing app in China).

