## Assignment of interventions

Once recruitment is completed, eligible participants will be randomly allocated to either iMBCT-I group or SHE group with an allocation ratio of 1:1, using simple randomization facilitated by computer-generated random numbers in IBM SPSS 25.0 (66). The generated sequences will be placed in a sealed, opaque, identical-looking envelope, ensuring that the evaluator is unaware of the allocation. The study coordinator will assess baseline information and then inform the attending physician to refer participants to a research team. The study coordinator will not recruit participants.

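### The primary ISI comparison between two independent arms is assigned paired tests, and the valid regression beside it is not named as decisive

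*Protocol article*

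**What the plan says.** The design is two separate groups: "This is a prospective, parallel-group, exploratory randomized (1:1 allocation ratio) controlled study" (Trial design). Allocation is made "using simple randomization facilitated by computer-generated random numbers in IBM SPSS 25.0" (Assignment of interventions), and no matching is described.

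Primary outcome analysis gives two analyses of ISI change to week 8.

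- The first is a test: "Changes between groups in ISI scores from baseline to week 8 will be evaluated using paired t-tests (for normally distributed data". For other data it offers "paired Mann-Whitney U tests (for non-normally distributed data".
- The second is a model: "A Univariable linear regression will be conducted to evaluate the effect of MBCT-I on ISI score reduction". In it, "the intervention group (MBCT-I vs. SHE) will be included as the independent categorical variable", and the coefficient is taken as the treatment effect.

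The section does not say which of the two decides the trial.

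Secondary outcome analysis lists the questionnaire scores, the remission rate and the sleep parameters, and says their changes "from baseline to week 8 will be evaluated using paired t-tests (for normally distributed data)/Mann-Whitney U tests". Here the Mann-Whitney test is no longer called paired.

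**The concern.** A paired test needs a natural link between the two values in each pair. A participant's baseline and week-8 scores are linked. A participant in one arm and a participant in the other are not. The paired t-test can therefore be run meaningfully only within an arm, and that does not answer a question about differences between groups. The Mann-Whitney U test is the independent-samples rank test; its paired counterpart is the Wilcoxon signed-rank test. The stated non-parametric option combines two incompatible things.

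At stake is what the primary p-value would measure. A within-arm test picks up everything that changes over eight weeks: regression to the mean after selecting on ISI above 14, natural course, and attention. The plan itself expects the SHE arm to improve by 3.1 points. The Blinding section also says that the analyst will not know the study hypotheses or the randomisation procedures, so that person has to rely on the written instruction.

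**Working it through.** **Inputs.** From Sample size: expected ISI reductions 7.7 (iMBCT-I) and 3.1 (SHE), common SD 5.5, alpha 0.05, power 0.90, 30 per group, 20% dropout, 80 in total. From Statistical methods: two-tailed testing. Assumption: 5.5 is the SD of the change in ISI. The article does not say so, but gives it alongside the reductions.

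**1. Which comparison was the trial sized for?** The difference is 7.7 − 3.1 = 4.6.

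- Independent two-sample, normal approximation: n per group = 2 × [5.5 × (1.960 + 1.282) / 4.6]² = 30.04. This matches the stated 30 to within rounding.
- Exact t calculation: 32 per group, and 64 / 0.80 = 80, the planned total.
- One-sided two-sample: 25 per group. A single paired sample with the same 4.6 and 5.5: 18. Neither gives 30.

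Of these, only the two-sided independent comparison gives the stated figure.

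**2. What does a within-arm paired t-test do when there is no treatment difference?** Suppose both arms improve by the same amount c. The test in the iMBCT-I arm has noncentrality c / (5.5 / √n). The probability of p < 0.05 from the noncentral t distribution is:

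| Shared change c | n = 32 | n = 40 |
|---|---|---|
| 1 point | noncentrality 1.03, 17% | 1.15, 20% |
| 2 points | 2.06, 51% | 2.30, 61% |
| 3.1 points | 3.19, 87% | 3.56, 94% |

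A nominal 5% test of iMBCT-I against SHE should give 5% in every cell.

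**3. Other ways to carry out the paired wording.**

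- Calling the trial positive when iMBCT-I is significant and SHE is not: 11.3% at 32 per arm and 6.1% at 40, with a shared change of 3.1 (20,000 simulated trials).
- Pairing participants across arms arbitrarily: type I error stays near 5% (4.8% and 5.1%). The pairing has no meaning and needs equal arms; under simple randomisation of 80, an exact 40:40 split has probability C(80,40) / 2⁸⁰ = 0.089.

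**4. The correct test.** With equal variances, the independent-samples t-test on change is identical to the univariable regression already planned. Simulated type I error is 4.9% at 32 per arm and 5.2% at 40. Power for 4.6 with SD 5.5 is 89.0% at 30, 90.9% at 32 and 95.9% at 40 per arm.

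**The case against.** The best reply is that this is a slip in naming, and much supports it. The sentence speaks of changes between groups, and the section also asks for a between-group effect size. The regression on group follows at once. The Sensitivity analysis section adjusts that regression for baseline ISI, and the secondary section adds a mixed model for ISI with a treatment-by-time term. The sample size points the same way, and the secondary section drops the word paired before Mann-Whitney. All of this stands, and it makes a deliberate within-arm plan unlikely.

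A reader might infer that the randomised comparison is lost, or that the trial has a false-positive rate of about 90%. The documents do not support either. A valid between-arm estimate is prespecified in the same section. The highest figures need a within-arm reading, a full 3.1-point shared change, 5.5 as the SD of change, and the regression ignored.

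A reader might also object that the primary hypothesis names no comparator: "The primary hypothesis for this trial is that the iMBCT-I will reduce insomnia severity by the end of the treatment (8 weeks". The same Introduction says that effectiveness is judged by comparison with SHE, so rewording it is a preference.

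Finally, the choice of the decisive analysis may be made in a statistical analysis plan that is not shown. That softens the point about designation. It does not correct the tests that this article does name.

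**Conclusion.** The point holds as an error in the stated primary test. The article assigns paired tests to a comparison of independent arms, names one test that does not exist, and repeats the paired t-test for the secondary outcomes. There it reaches binary remission, which the planned mixed models do not cover. The regression of ISI change on group is sound and protects the comparison if it is used, but it comes second and is not designated.

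The size depends on what is done with the wording. If the regression decides, there is no inflation. If a within-arm paired test in 40 iMBCT-I participants were taken as the primary result, the chance of a significant finding without any treatment difference would be about 20%, 61% and 94% for shared changes of 1, 2 and 3.1 points. Those figures assume normally distributed changes with SD 5.5.

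**What to change.** In Primary outcome analysis, replace the paired tests in one of two ways:

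- use an independent-samples t-test, or an ordinary Mann-Whitney U test, on the change in ISI; or
- make the regression of ISI change on group the single primary analysis, preferably adjusted for baseline ISI. That score is already collected and is already a covariate in the Sensitivity analysis section.

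State which analysis decides the trial. In Secondary outcome analysis, make the same replacement for the continuous outcomes, and use a test for proportions or logistic regression for remission. Report within-arm changes descriptively only.

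The cost is a change of wording in the protocol, and in the statistical analysis plan if it carries the same text. No extra data, participants or procedures are needed, and the sample size stays at 80.
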